## Abstract

**Background:**

Dentin hypersensitivity (DH) is a condition characterized by short and sharp episodes of pain which will arise in response to tactile, chemical, thermal, evaporative or osmotic stimuli. The painful symptoms cause discomfort in patients and reduce their quality of life. Recently, the novel zinc-containing desensitizer CAREDYNE Shield has been developed as a new type of desensitizer that acts by inducing chemical occlusion of dentinal tubules, and releasing zinc ion for root caries prevention. However, the clinical effectiveness of CAREDYNE Shield on DH remains unclear. Therefore, the aim of this study is to evaluate the effectiveness of CAREDYNE Shield on DH by comparing with that of another desensitizer, Nanoseal, commonly used in Japan.

**Methods/design:**

This study protocol is a two-arm, parallel, pilot randomized controlled trial. Forty DH patients will be randomly allocated to two groups. Participants in the intervention group will be treated with CAREDYNE Shield, while those in the control group will be treated with Nanoseal. The primary outcome is the reduction of pain intensity in response to air stimuli measured with a 5-point verbal response scale from baseline to 4 weeks after the intervention, and Fisher’s exact test will be used for analyses.

**Discussion:**

CAREDYNE Shield can be casually applied to subgingival areas and proximal surfaces because it reacts with only tooth substance. Furthermore, zinc has been reported to reduce the demineralization of enamel and dentin and inhibit biofilm formation, plaque growth and dentin-collagen degradation. Therefore, CAREDYNE Shield may be expected to be a useful novel desensitizer that acts not only as a desensitizer but also as a root caries inhibitor.

**Trial registration:**

UMIN Clinical Trials Registry (UMIN-CTR), ID: UMIN000038072. Registered on 21 September 2019.

**Trial status:**

This study (protocol version number: version 1.4.0; approved on 22 October 2019) is ongoing. The recruitment of participants began in December 2019 and will be continued until November 2020 (Hanke, Am Dent Assoc 27:1379–1393, 1940).

## Background

Dentin hypersensitivity (DH) is a condition characterized by short and sharp episodes of pain which arise in response to tactile, chemical, thermal, evaporative or osmotic stimuli, and which cannot be ascribed to any other form of dental defect or pathology [1, 2]. A recent systematic review reported the DH prevalence in various population to range from 1.3 to 92.1%, and the estimated DH prevalence analyzed in a random-effects meta-analysis was 33.5% (95% confidence interval 30.2–36.7%) [3]. The painful symptoms cause discomfort in patients and reduce their quality of life [4].

Normally, dentin is covered by enamel or cementum and is not affected by direct stimuli; however, once the dentin has been exposed and dentinal tubules are patent in the oral environment, the painful symptoms of DH arise in response to external stimuli. Dentin exposure results from a loss of enamel or cementum. The loss of enamel can be attributed to erosion, abrasion or abfraction, while the loss of cementum is caused by gingival recession associated with improper tooth-brushing, periodontal disease and periodontal surgery.

A number of theories have been suggested to explain the mechanisms of DH; however, the hydrodynamic theory has been widely accepted [5, 6]. According to this theory, fluid movement in the patent dentinal tubules occurs in response to external stimuli, stimulating sensory nerve endings located at the dentin-pulp interface. Thus, dentinal tubule occlusion, which reduces the fluid movement in the dentinal tubules, is one of the ideal DH treatments and is performed with adhesive systems or desensitizing agents that form insoluble mineral precipitates in the patent dentinal tubules [7].

One of desensitizing agents which form insoluble mineral precipitates in patent dentinal tubules is the fluoroaluminocalciumsilicate-based desensitizer Nanoseal (Nippon Shika Yakuhin, Yamaguchi, Japan). The components are similar to those of silicate cement. Nanoseal acts as a desensitizer by a chemical reaction resulting in insoluble nanoparticles that aggregate on the tooth surface for dentinal tubule occlusion and has been suggested to protect the root surface from demineralization via ions, such as calcium or fluorine, released from Nanoseal [8–10]. Thus, Nanoseal may act not only as a desensitizer but also as a root caries inhibitor.

Recently, the fluorozinccalsiumsilicate-based desensitizer CAREDYNE Shield (GC Dental Industrial Corporation, Tokyo, Japan) has been developed. It acts as a desensitizer by inducing chemical occlusion of dentinal tubules and contains a novel functional filler that releases not only ions, such as calcium and fluorine, but also zinc. Zinc has been reported to reduce the demineralization of enamel and dentin, and inhibit dentin collagen degradation, plaque growth and biofilm formation [11, 12].

However, the effectiveness of CAREDYNE Shield on DH still remains unclear; therefore, the aim of this study is to investigate the effectiveness of CAREDYNE Shield on DH by comparing with that of Nanoseal. The PICO question of this study is described in Table 1.

**Table 1 Tab1:** PICO question

**Criteria**	**Description**
P (participants)	Non-carious human permanent teeth with DH
I (Intervention)	DH treatment with CAREDYNE Shield
C (Control)	DH treatment with Nanoseal
O (Outcome)	The reduction of pain level in response to air stimuli

*DH* dentin hypersensitivity

## Methods/design

### Trial design

This study protocol is a two-arm, parallel, pilot randomized controlled trial; that was developed in accordance with the Standard Protocol Items: Recommendations for Interventional Trials (SPIRIT) and Consolidated Standards of Reporting Trials (CONSORT) guidelines [13, 14]. A SPIRIT Checklist is attached in Additional file 1.

### Participant timeline

To describe the time schedule of enrollment, intervention and assessment, a SPIRIT Figure and a CONSORT flow chart are presented in Table 2 and Fig. 1.

**Table 2 Tab2:** Standard Protocol Items: Recommendations for Interventional Trials (SPIRIT) Figure

	**Enrollment**	**Post allocation**
**Time point**	0	4 weeks (range 3–5 weeks)
**Enrollment:**		
Eligibility screen	X	
Informed consent	X	
Allocation	X	
**Intervention:**		
CAREDYNE Shield	X	
Nanoseal	X	
**Clinical assessment:**		
Air blow	X	X
Inspection	X	X
Palpation	X	X

**Fig. 1 Fig1:**
[figure not shown]
Consolidated Standards of Reporting Trials (CONSORT) flow chart

### Study setting

All procedures of this study will be performed at the Department of Periodontology and Endodontology, Nagasaki University Graduate School of Biomedical Sciences, Nagasaki, Japan.

### Sample size

No previous clinical studies have investigated the effectiveness of CAREDYNE Shield on DH; therefore, at least 15 participants will be required in each group to perform a sample size calculation in a subsequent study [15]. With a 20% dropout rate, a total of 40 participants will be recruited in this study.

### Eligibility screen

When patients present with DH complaints at Nagasaki University Hospital, clinical diagnosis will be performed by the dentist in charge of the patient. Short and sharp pain episodes of pain which arise in response to air stimuli or tactile stimuli will be assessed with a three-way dental syringe or a dental explorer, caries or restoration will be assessed with a dental mirror and a dental explorer, severe periodontal diseases will be assessed with a dental mirror and a periodontal probe and the information about medical/dental history will be obtained by interview. Then, the eligibility criteria described in Table 3 will be verified.

**Table 3 Tab3:** eligibility criteria

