**Inclusion criteria**	
Outpatients	
Participants who presented with a DH complaint	
Participants who agreed to participate in this study after providing their informed consent	

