**Exclusion criteria**	
Participants who have an allergy to the desensitizing materials used in this study	
Participants who are pregnant or lactating	
Participants who have undergone DH treatment within the last 6 months	
Participants with systemic diseases that might influence the results of this study	
Participants who present with pain complaints that might influence the results of this study	
DH teeth with restoration that might influence the results of this study	
DH teeth with caries or advanced periodontal disease	
DH teeth that have undergone periodontal surgery or orthodontic treatment within the last 3 months	

*DH* dentin hypersensitivity

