### Primary outcome

The primary outcome is the reduction of pain intensity in response to air stimuli measured with a 5-point verbal rating scale (VRS) from baseline to 4 weeks after the intervention. To evaluate the pain level, an air blast will be applied using a three-way dental syringe after the isolation of the DH teeth with cotton rolls, participants will then be asked verbally to rate the level of pain intensity using a 5-point VRS (numerical scale from 0 to 4 summarized in Table 5).

**Table 5 Tab5:** Verbal rating scale

**Score**	**Level of pain intensity**
0	No pain
1	Mild pain
2	Moderate pain
3	Severe pain
4	Extremely intense pain

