## Discussion

Several limitations associated with the present study warrant mention. First, blinding of operators will not be performed; therefore, the risk of bias in this domain may be unavoidable. Second, the data will be collected just after the participant’s training. Thus, VRS which is easier to understand for participants than a visual analog scale (VAS) will be performed; however, VRS is considered to be less sensitive than VAS [18, 19]. Third, it has been recommended that at least three different stimuli, specifically tactile, cold and air stimuli, should be used for clinical assessments of DH because DH may differ among stimuli [2]. However, only air stimuli will be evaluated in the present study because this study is being performed for sample size calculations, which is based on the primary outcome: the reduction of pain intensity in response to air stimuli. Tactile stimuli will be evaluated as a secondary outcome in a future, large-scale study. The GI and PI will be used as secondary outcomes in the present study. If a reduction in either is observed, the effectiveness of CAREDYNE Shield for the reduction of the GI and PI will be investigated in a future clinical study.

Desensitizers like CAREDYNE Shield and Nanoseal that induce chemical occlusion of dentinal tubules are biocompatible and react only with tooth substance; they can, therefore, be casually applied to subgingival areas and proximal surfaces. Furthermore, for several decades, in-vitro studies have investigated the function of zinc and reported that zinc reduced the demineralization of enamel and dentin and inhibited dentin collagen degradation, plaque growth and biofilm formation [20–24]. Thus, CAREDYNE Shield, which releases zinc ions, may be a useful novel desensitizer that acts not only as a desensitizer but also as a root caries inhibitor.

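### Patients sensitive only to touch can be enrolled, although the sole pain outcome is the fall in an air-blast score that may already be 0 at baseline

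*Protocol article*

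**What the plan says.** **Entry.** In the Eligibility screen section, "pain which arise in response to air stimuli or tactile stimuli will be assessed with a three-way dental syringe or a dental explorer". The inclusion criterion in Table 3 that concerns the condition reads "Participants who presented with a DH complaint". The one exclusion criterion that mentions pain, "Participants who present with pain complaints that might influence the results of this study", is aimed at pain that could interfere with the results. It does not address a lack of response to air.

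**Sequence.** Under Informed consent and Randomized allocation, an examiner blinded to allocation enrols the patient and takes the baseline measurements. The treating dentist then opens the envelope. No baseline score stands as a condition between these steps.

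**Outcome.** "The primary outcome is the reduction of pain intensity in response to air stimuli measured with a 5-point verbal rating scale (VRS) from baseline", with the second assessment at 4 weeks; the scale is a "numerical scale from 0 to 4 summarized in Table 5", where 0 means no pain. The Discussion confirms that "only air stimuli will be evaluated in the present study because this study is being performed for sample size calculations". It defers tactile response to a later study and accepts that sensitivity can vary from one stimulus to another.

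**Analysis.** Statistical design names Fisher's exact test for the primary outcome and rules out any additional analysis.

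**The concern.** The entry rule and the outcome use different stimuli. A tooth that reacts to the explorer but not to the air syringe meets the written criteria, yet its baseline score on the outcome scale is 0. From 0 the score can only stay or rise, so even complete relief of the patient's actual complaint produces no reduction.

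What is at stake is the purpose of the pilot. Sample size and Discussion both say that it is run to support a sample size calculation for a later study, based on the air outcome. Patients who cannot show that outcome use up places among the 40 and pull the observed difference between arms towards zero. Because additional analyses are ruled out, no planned analysis would separate them.

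**Working it through.** **1. The plan's own figure.** Sample size gives at least 15 per group, 20% dropout and 40 in total.

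- 15 / (1 − 0.20) = 18.75, rounded up to 19 per arm, or 38 in total. The stated 40 fits this with rounding up to 20 per arm.
- Multiplying instead gives 15 × 1.20 = 18 per arm, or 36, which does not match.
- Expected completers: 20 × (1 − 0.20) = 16 per arm.

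**2. Completers able to improve.** Let f be the share entering with air VRS 0. The documents do not give f, so a range is shown. If dropout is unrelated to f, the expected number able to improve is 16 × (1 − f) per arm. It equals 15 at f = 1 − 15/16 = 6.25% and is lower beyond that.

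**3. Chance that it happens at all.** P(at least one of 40 enters at 0) = 1 − (1 − f)^40.

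**4. Dilution.** If a patient at 0 is classed as not reduced, a response proportion p among air-responsive patients is observed as (1 − f)p. A difference p1 − p2 is observed as (1 − f)(p1 − p2). As an example, assume 80% against 40% among air-responsive patients. The table adds two illustrative quantities:

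- exact power of Fisher's test at 16 per arm, two-sided 0.05 (assumed), by enumeration;
- the n per arm that a later trial would project from the observed rates at 80% power, n = [1.96√(2p̄(1 − p̄)) + 0.842√(p1(1 − p1) + p2(1 − p2))]² / (p1 − p2)², with p̄ the mean of p1 and p2.

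| f | Able to improve per arm (of 16) | P(at least one of 40 at 0) | Observed rates | Difference | Fisher power | Projected n per arm |
|---|---|---|---|---|---|---|
| 0 | 16 | 0 | 80% v 40% | 40 points | 0.505 | 23 |
| 5% | 15.2 | 0.871 | 76% v 38% | 38 points | 0.449 | 26 |
| 10% | 14.4 | 0.985 | 72% v 36% | 36 points | 0.399 | 29 |
| 20% | 12.8 | over 0.999 | 64% v 32% | 32 points | 0.310 | 38 |
| 30% | 11.2 | over 0.999 | 56% v 28% | 28 points | 0.232 | 48 |

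Only 15, 20% and 40 come from the protocol. The share f, the response rates, the significance level, the sidedness and the 80% power are assumptions.

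**The case against.** Several points on the other side have force.

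- **No such patient is documented.** A reader might infer that some participants will enter at 0. The article gives no touch-only share and nowhere says that such patients are deliberately accepted. What stands is that the written rules allow them. The full protocol could hold a threshold, but Table 3 is presented as the eligibility criteria, and the mismatch lies in what is printed.
- **No responder rule is stated.** A reader might infer that a 0-to-0 patient counts as a failure in Fisher's test. The article defines no cut-off, so that classification is an assumption in the working. It remains true that the patient cannot show a reduction.
- **The pilot has no power target.** Its size rests on 15 per group, and the article does not say that each of the 15 must be able to improve. The 6.25% figure is therefore a benchmark, not a breach of a stated rule. The power column is illustrative only.
- **A general inflation factor is tempting.** Scaling the sample size by 1/(1 − f)² (1.23, 1.56 and 2.04 at 10%, 20% and 30%) assumes a comparison of means at constant standard deviation. The planned test is Fisher's. Even for means, patients with zero change make the arm variance (1 − f)s² + f(1 − f)m², where m and s are the mean and standard deviation of the reduction in air-responsive patients. That can be above or below s².
- **Bias in the next trial's planning depends on its entry rule.** If that trial admits the same mix, the diluted difference is the right planning value. It misleads only if entry is then limited to air-responsive patients, and the documents do not say which will apply.
- **Allocation is random.** A reader might infer a systematic bias between arms. Any imbalance in patients at 0 would arise by chance, although chance imbalance is quite possible at 20 per arm.

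**Conclusion.** The concern holds as a mismatch between who can enter and what is measured. The written rules allow randomisation of patients with a baseline air score of 0, who cannot show the primary outcome, and nothing else in the article closes the gap. The consequence is dilution and lost information: the pilot's estimate understates the effect in patients able to respond.

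The size depends on f, which is unknown. A difference in response proportions shrinks by (1 − f) if patients at 0 are classed as not reduced. The expected number of completers able to improve falls below 15 per arm once f exceeds 6.25%, if 20% drop out regardless of air score. The article does not support saying that such patients are certainly enrolled, that the arms are systematically biased, or that the later trial's sample size will necessarily be wrong.

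**What to change.** **Eligibility.** Add to Table 3: air-blast VRS of at least 1 on the DH tooth to be treated, checked by the blinded examiner at the baseline assessment, after consent and before the envelope is opened. The measurement is already taken at that point, so no new procedure is needed. Because enrolment currently precedes it, the text should also say that a patient scoring 0 is not randomised. If more than one tooth is treated, the criterion should apply to the tooth whose score enters the analysis.

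**Participants already randomised.** The article says that recruitment is under way. For anyone randomised with a baseline air VRS of 0, define the primary analysis set by that pre-allocation value, and report how many were excluded in each arm. The value itself cannot depend on allocation, but the rule must be fixed before anyone sees outcomes by arm. It narrows the set analysed under the stated intention-to-treat principle, and the report should say so.

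**Cost.** A few consented patients are not randomised, recruitment is slightly slower, and the results apply to air-responsive DH only.

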**Inclusion criteria**	
Outpatients	
Participants who presented with a DH complaint	
Participants who agreed to participate in this study after providing their informed consent	
**Exclusion criteria**	
Participants who have an allergy to the desensitizing materials used in this study	
Participants who are pregnant or lactating	
Participants who have undergone DH treatment within the last 6 months	
Participants with systemic diseases that might influence the results of this study	
Participants who present with pain complaints that might influence the results of this study	
DH teeth with restoration that might influence the results of this study	
DH teeth with caries or advanced periodontal disease	
DH teeth that have undergone periodontal surgery or orthodontic treatment within the last 3 months	

*DH* dentin hypersensitivity

### Informed consent

After eligibility screen, the potential participants who met the eligibility criteria will be asked for their informed consent using the informed consent form. They will be then enrolled in this study by an examiner blinded to the allocation. A signed informed consent form is mandatory for enrollment.

### Randomized allocation

After enrollment, baseline assessments will be performed by the examiner who enrolled the participant in this study. Randomized allocation will then be performed in a 1:1 ratio by the dentist in charge of the patient with opaque, sealed envelopes prepared before participant recruitment and on which “Nanoseal” or “CAREDYNE Shield” is printed. Participants allocated to the intervention group will be treated with CAREDYNE Shield, while those allocated to the control group will be treated with Nanoseal. The information on the desensitizers used in this study is described in Table 4.

**Table 4 Tab4:** Desensitizers used in this study

**Material**	**Manufacturer**	**Composition**
CAREDYNE Shield	GC Dental Industrial Corporation, Tokyo, Japan	Solution A: fluorozinccalciumsilicate glass Solution B: 10–15% phosphoric acid
Nanoseal	Nippon Shika Yakuhin Co., Ltd., Shimonoseki, Japan	Solution A: fluoroaluminocalciumsilicate glass Solution B: 10% phosphoric acid

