### Allocation concealment

After the allocation, the operator who performed allocation will record the operator’s name, baseline date and type of teeth to be treated in the allocation list. The list will not contain the allocated group name in order to conceal the allocation as well as the participant’s name and ID number for personal information protection. Allocation information will be recorded in the electronic medical record system which research staff cannot check without leaving a record of their browsing history.

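### As written, the allocation envelopes carry the treatment name, which defeats concealment from the dentist who makes the screening diagnosis, allocates and treats

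*Protocol article*

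**What the plan says.** The steps, in the order the protocol article gives them:

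- *Eligibility screen*: "clinical diagnosis will be performed by the dentist in charge of the patient". The patient's response to air or tactile stimuli is tested at this stage. Next, "Then, the eligibility criteria described in Table 3 will be verified"; the article does not say by whom.
- *Table 3*: three of the exclusions rest on judgement, for example "Participants with systemic diseases that might influence the results of this study". The other two, on pain complaints and on restorations, use the same qualifier.
- *Informed consent*: "They will be then enrolled in this study by an examiner blinded to the allocation".
- *Randomized allocation*: "After enrollment, baseline assessments will be performed by the examiner who enrolled the participant in this study". After that, "Randomized allocation will then be performed in a 1:1 ratio by the dentist in charge of the patient", using "opaque, sealed envelopes prepared before participant recruitment and on which “Nanoseal” or “CAREDYNE Shield” is printed".
- *Allocation concealment*: "After the allocation, the operator who performed allocation will record the operator’s name, baseline date and type of teeth to be treated". The list leaves out the group name and the participant's identity. The arm is entered in the electronic medical record, where access leaves a trace.
- *Intervention*: the operator who allocated also treats. Cleaning, rinsing, isolation and drying are described after allocation and are the same for both arms.
- *Discussion*: operators are not blinded, and this is listed as a limitation.

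**The concern.** Concealment means that nobody deciding whether, or when, a patient enters the trial can know the next assignment. It is what makes the two arms comparable at the start, and analysis cannot restore it afterwards. An opaque, sealed envelope serves this purpose only if the assignment is inside. Here the sentence describing the envelopes puts the treatment name on them and hands them to a dentist who has already examined the patient.

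At stake is the comparability of the arms in a pilot of 40 participants whose results are meant to inform the sample size of a later study. A second, smaller matter follows from the same step. Because the arm is known before the tooth is cleaned and dried, preparation is done by someone aware of the assignment, and one secondary outcome is the Plaque Index at the treated surface.

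**Working it through.** This is a point of procedure, so the check sets the sections side by side. The only design figure is the sample size: 15 / (1 − 0.20) = 18.75, rounded up to 19 per group, or 38 in total. The plan's 40 gives 40 × 0.80 / 2 = 16 completers per group, at least the 15 required. That figure is sound, and nothing below depends on it.

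1. **Does the envelope hide the arm?** *Randomized allocation* gives two properties in one sentence: sealed and opaque, and bearing the product name. If the name is on the envelope, its holder knows the arm with certainty. The two properties cannot both serve concealment.

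2. **Who could use that knowledge?** One role appears three times: the dentist in charge makes the screening diagnosis (*Eligibility screen*), allocates (*Randomized allocation*) and, as the operator, treats (*Intervention*).

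3. **By what route?** The article does not say whether envelopes are taken in a fixed order. If they are, the next arm is visible during screening, and a patient could be put forward or held back; the judgement-based exclusions in Table 3 leave room for this. If they are not, the dentist could choose the envelope at allocation. One of the two routes is open in either case.

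4. **What do the blinded steps close?** Enrolment and baseline assessment are done before allocation by an examiner unaware of the arm (*Informed consent*, *Randomized allocation*). This protects the baseline scores and means that an enrolled patient can no longer be screened out. Screening comes before these steps and envelope choice comes after them, so neither is covered.

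5. **Does *Allocation concealment* close the rest?** Its first words place it after allocation. Leaving the group off the list and logging access to the medical record help keep research staff unaware of arms already assigned. They do not hide the next one. The article describes no check that envelopes were used in order.

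6. **When does the operator learn the arm?** *Intervention* places tooth preparation after allocation. As preparation is common to both arms, it could be finished before the envelope is opened.

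**The case against.** The strongest reply is that sealing and opacity make sense only if the assignment is inside, so the phrase about printing may be a loose description of the contents. That may well be so. The text does not say it, however, and a sentence that misdescribes the central randomization step still needs correcting.

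A second reply is that numbering, marking and retention of envelopes are details an article may leave to the full protocol. This is fair: their absence is not the point. The point is a stated procedure that works against its own purpose.

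A third is that unblinded operators are already disclosed and that one preparation procedure applies to both arms. This also stands. Different preparation by arm is a possibility only, and it is a matter of performance rather than concealment. It bears on when the envelope is opened and is no separate finding.

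A reader might go further and infer three things that the documents do not support:

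- *That the dentist decides eligibility.* The article gives the diagnosis to the dentist but does not name who verifies the criteria.
- *That steering would leave no trace.* The arm is in the medical record, and the assessment form holds the baseline pain score, date and tooth type, so an imbalance at baseline could be seen. Only a check of envelope order is not described.
- *That the bias can be sized.* Nothing in the article says how many patients might be steered or how the sequence was generated, so any figure would be invented.

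**Conclusion.** The concern holds in this form: followed as written, the envelope procedure does not conceal the next assignment from the dentist who makes the screening diagnosis and allocates, and the section on concealment does not repair it. The blinded examiner limits the exposure to two places, screening and the choice of envelope.

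This rests on the literal reading of one sentence. If the name is in fact on a card inside, the defect is one of wording. A reader might conclude that the arms are already biased; the article gives no evidence of that, and selection bias is possible rather than shown. No numerical size can be attached. The matter should be settled before further participants are allocated, because concealment cannot be recovered later.

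**What to change.** First establish what is printed where.

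- **If cards are already inside the envelopes**, correct the sentence in *Randomized allocation* to say so.
- **If the name is on the envelope**, print it only on a card inside plain, sequentially numbered, opaque sealed envelopes. Use them strictly in number order, and write the study number and date on each one before opening it. Keep the opened envelopes so that the staff member who already does the monitoring can check them against the sequence.
- **In both cases**, open the envelope after the baseline assessment and after the cleaning, isolation and drying common to both arms, so that preparation is finished before the operator knows the arm.

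The article reports that recruitment started in December 2019, so new envelopes cannot change assignments already made. Apply the change to the remaining participants, and report which participants were allocated under the procedure now described.

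The cost is a short amendment and at most 40 new envelopes, assuming one per participant, with no extra staff. The small drawback is that the envelope is opened at the chairside just before mixing, which must be done out of the participant's sight to keep the participant blinded.
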